**Figure 7 fig7:**
[figure not shown]
Schematic diagram of clinical measurements and biological monitoring.

#### Urine sampling

3.2.2

During IP1 and IP2, two urine samples are collected from each participant, the first on Monday morning of Week 1 and the second on Friday afternoon of Week 2 (Figure 7). To directly correlate their external exposure to internal dose, a stratified, data-driven strategy is employed for targeted biomarker analysis. The selection of urinary biomarkers of exposure will be informed by the results of the preceding air samplings. For example, if certain compounds (e.g., benzene or pyrene) are consistently detected or show significant variance during the air sampling campaigns, their corresponding specific biomarkers of exposure (e.g., SPMA for benzene and 1-OHP for pyrene) will be quantified via GC–MS or LC–MS/MS. This allows for precise assessment of children’s internal dose and direct correlation with the measured school environment. Additionally, samples will be screened for general biochemistry and contaminants. Country-specific protocol variations apply, as ethical and regulatory restrictions preclude urine collection in Greece. To address the impact of these biomonitoring variations across cohorts, environmental monitoring will serve as the primary, standardized exposure metric to link with health outcomes (as described in Section 4) for pooled exposure-response analyses of the entire cohort across the three countries. Analyses relying on urinary biomarkers will be stratified and limited to the Belgian and Danish cohorts to further investigate internal exposure pathways and complement environmental data.

## Health outcomes

4

To investigate the health impact of IAQ and the planned intervention, cognitive performance and blood pressure (BP) are assessed as primary outcomes at multiple time points. Additionally, clinical examinations evaluate secondary outcomes, including psychological well-being, anthropometric measurements, and the skin microbiome. All measurements are performed in an examination room provided by the participating school. The examination room is appropriately lighted and ventilated. A CO₂ measuring device is placed to monitor air quality levels. CO₂ levels are regulated by opening windows and doors at appropriate times. Two testing days are scheduled at BaP. The subsequent testing days occur on the final day of IP1 and the final day of IP2 (Figure 7).

### Questionnaires on background information, mental health, and indoor air quality in schools

4.1

Four questionnaires are provided to collect general information regarding the lifestyle and living situation, mental health, and well-being of the child. The first of these, focusing on the baseline parameters detailed in Table 3, is to be completed by parents or guardians prior to the start of the BaP.

**Table 3 tab3:** Information provided by parents/guardians of the participant in the questionnaire.

Category	Parameters
Personal information	Child full name Class and school Parent email Birthdate Sex
Parental information & socioeconomic status	Respondent relation Country of birth Highest eduction Occupation Financial situation Home ownership status
Demographic/residential information	Current living address(es) (duration) Previous living address(es) (duration) Home heating systems
Environmental exposures	Household smoking status Transport type (time) Exposure to busy traffic Household noise exposure
Health and medical history	General Health Chronic condition Respiratory health Medication/supplement use Allergies
Early life exposures	Birth order Birth weight Birth method Address during pregnancy Complications pregnancy Gestational age Smoking status pregnancy Breastfeeding
Lifestyle and physical activity	Physical activity (type, duration) Indoor/outdoor play time Screen time Sleep duration and quality Eating habits

Two additional questionnaires are completed by the children on the measuring days at the end of IP1 and IP2: the Kidscreen-27 (49) and the Strengths and Difficulties Questionnaire (SDQ) (50) (Figure 7). The Kidscreen-27 is an instrument with 27 items that measure 5 parameters: physical activity and health, feelings and self-image, family and leisure, friends, and school and learning. It takes around 15 min for the children to complete this questionnaire, which is done in a calm environment. The SDQ is a screening list of 25 items that measures 5 parameters: hyperactivity/attention deficit, problems with peers, emotional problems, prosocial behavior, and behavioral problems. The questionnaire also takes 15 min to complete and measures the presence of psychosocial problems, the strengths of the child, and the influence of psychosocial problems on daily functioning.

The final questionnaire is administered on the second measuring day of the BaP, as well as on the testing days of IP1 and IP2 (Figure 7). This questionnaire assesses subjective perceptions of IAQ (SIAQ) in the classroom. Children are asked to evaluate the air quality, report any experienced symptoms, and indicate whether they perceive any thermal discomfort or noise disturbances potentially associated with the study devices or the ventilation system.

The study utilizes both established and project-specific measures: the highly validated Kidscreen-27 (51) and SDQ (52) are available in multiple languages, whereas the baseline questionnaire and SIAQ were tailored specifically for the LEARN project and translated into Greek, Danish, and Dutch by native speakers.

### Blood pressure and anthropometric measurements

4.2

Since air pollution exposure can affect BP (8, 53), BP is measured at the end of the BaP, as well as on the measuring days of IP1 and IP2 (Figure 7). To account for 24-h BP variability (BPV) (54), all measurements are performed between 08:00 and 12:00 h consistently. Children are asked to rest for 15 min. Afterward, the measurements are conducted on the non-dominant arm. Systolic BP (SBP), diastolic BP (DBP), and heart rate (HR) are noted down. The exact time of each measurement is recorded, along with the initials of the researcher conducting the assessment and possible deviations in the standard operating protocol (SOP). An automated BP instrument (Omron M3 comfort) is used to make five consecutive BP readings (1 min in between) using a pediatric cuff with the correct size. The first two measurements serve to acclimate participants to the environment and minimize stress. The final three readings will be averaged to adjust for any remaining stress-related fluctuations and used for the analysis. Additional measurements might be necessary if errors occur.

Additionally, anthropometric measurements, including height, weight, and waist circumference, are recorded at BaP. Height is measured using the SECA 213 stadiometer. Children are asked to remove their shoes and socks and stand in a freely upright position. Weight is measured using an Omron BF511 body composition monitor. Waist circumference is measured with a Seca 201 anthropometric tape. For this, the child is asked to make their belly button visible. These parameters, which can influence blood pressure, will be accounted for in the analysis (55). Any deviations from the SOP are noted down.

### Cognitive assessment

4.3

To assess the short-term effects of improved IAQ on cognitive function, a series of cognitive tests is performed on tablet devices under the supervision of trained staff. The program ‘Testmanager Minds’ is applied to conduct the tests (56). This is a software package for administering and scoring automated (neuro)psychological tests. Assessment instruments are provided in Dutch, Danish, and Greek. The Dutch version is validated and drawn from prior studies, while the Danish and Greek versions have been officially translated and approved by native-speaking scientists. All language adaptations were integrated in collaboration with the original program developer to ensure technical and linguistic accuracy. A revised standardized protocol for administering cognitive tests was developed and tested during the pilot. This updated protocol includes the addition of audio recordings, providing standardized test explanations for each participant. The audio recordings are provided using noise-canceling headphones. A secondary purpose of using noise-canceling headphones is to minimize ambient noise and environmental distractions during cognitive testing. Because this protocol is standardized across all subjects, study phases, and sites, the baseline testing conditions remain fully comparable, thereby neutralizing potential confounding effects on concentration and cognitive performance. Additionally, desk dividers are installed between the children to reduce visual distraction.

The cognitive tests are always performed in the following order:

Continuous Performance Test: This test measures a child’s sustained attention and concentration using alphanumeric stimuli. A series of letters appears on the screen for 500 ms each. The child must press the spacebar when they see the letter “A” followed by “X.” To ensure understanding, a practice round of 20 letters is given. If the child achieves at least 80% accuracy, they proceed to the main test, which consists of 300 letters. If not, the instructions are repeated, and a new practice round is provided. Key variables recorded include the mean reaction time and amount of correct answers.Symbol Digit Modalities Test: This test assesses the child’s ability to process information. The child is presented with 9 different symbols associated with the numbers 1 to 9. In the default setting, the participant is presented with a number of sequences of symbols for 90 s that have to be combined with the correct numbers. The child is presented with 10 practice symbols before the beginning of the test, in which mistakes are indicated and can be corrected. The participant can manually indicate the response on a virtual keypad. Key variables recorded include total latency and accuracy.Memory Span Task: This test evaluates the child’s short-term memory. It consists of two subtasks for sequences of numbers, both forward and backward, which are presented visually. An ascending sequence of digits is presented that should be reproduced in the same order in the Forward condition, and backward in the Backward condition. Sequences of a given sequence length are offered 2 or 3 times. If two sequences of the same length are reproduced correctly, the sequence length is increased by 1 element; for 1 error, the third sequence is offered as a ‘retake’. At 1 sequence correct out of 3 attempts, the subtask is aborted. Answers are typed in on a virtual keypad. This test does not include a practice round before the actual test begins. Key variables recorded include span length and response latency for both the forward and backward tasks.STROOP Task: This test measures the child’s selective attention. A total of four buttons are shown on the screen (red, blue, yellow, and green), and the names of these colors appear on the screen in the same or a different color than the name indicates. As fast as possible, the children need to press the button that indicates the color the word is shown in, ignoring the color that the name indicates. Before the beginning of the test, a total of 12 practice trials are given, followed by 48 test trials. The real test begins once the child achieves at least 80% accuracy. Key variables recorded include reaction time.Signal Detection Test (SDT): This test evaluates a child’s visual information processing speed. It assesses perceptual sensitivity and response bias through multiple short trials featuring alphanumeric stimuli. The goal is to quickly determine whether a target symbol (U) is present among distractors (V) in a two-choice task. Children respond “yes” if they see a U among the *Vs* and “no” if they do not. The test consists of 60 trials, including a 10-trial practice round. The real test begins once the child achieves at least 50% accuracy. Key variables recorded include sensitivity and response bias. However, in the pilot study, the tablets used for testing often lacked the processing power to run the SDT test software, leading to frequent interruptions or complete data collection failures. These technical issues compromised the test’s reliability and led to significant missing data. Consequently, the SDT was discontinued and will be excluded from the final analyses to ensure the overall robustness of the study’s conclusions.

Children perform the cognitive tests at four time points (Figure 7). During the BaP, each child completes all cognitive tests twice on different days to account for potential learning curve effects (57). Afterward, the children repeat the tests during the intervention and sham-intervention phases on the testing days to evaluate the impact of IAQ. To control for any residual learning effects, the specific intervention period will be included as a covariate in the mixed-model analysis. Cognitive testing is standardly performed between 08:00 and 12:00 h to account for variations in concentration dependent on the time of day (58, 59). The supervisor documents possible distractions and lapses in concentration. Children are given a score based on their attentiveness during the cognitive testing (0 = no problem, 1 = distracted, 2 = influenced by someone, 3 = external distractions, 4 = did not understand the task, 5 = bored, 6 = other). A score is assigned for each of the cognitive tests. Reasoning for the score is also noted down.

### Skin microbiome

4.4

On the same days as blood collection, between 08:00 and 12:00 h, skin microbiome samples are collected using eNat® swabs (designed for nucleic acid collection and preservation) hydrated with 0.9% NaCl solution (Figure 7). These samples will be stored at UBiLim until further processing and analysis. Country-specific protocol variations apply, as ethical and regulatory restrictions prevent collection in Denmark and Greece.

## Data management and statistical strategy

5

### Data collection methods

5.1

All data are collected by trained and certified researchers affiliated with the LEARN project team. Prior to data collection, all personnel involved received comprehensive training to ensure standardization and adherence to established SOPs for environmental and biological sample collection, clinical measurements, and cognitive assessments. After the sampling campaign at each school, each child will receive a certificate of participation, and each participating class will receive a new board game developed within the LEARN project to help children learn about IAQ in schools.

### Data management

5.2

The samples will be stored for 25 years after completion of the project; blood, urine, and skin swab samples will be stored in freezers at −80 °C in each country. At the end of the collection process, the biological samples are sent to Belgium for analysis and subsequent storage at UBiLim. The research is part of the LEARN project, which started in May 2022 and will be completed in 2026. Afterward, the samples will be securely disposed of, and the data will be transferred to and stored on a secure data hub, which will be established in collaboration with our partners at Envirometrics S. A., so that all data will be available for at least 15 years after the publication of the results or the end of the funding period. Personal data will be stored until the conclusion of the project. Completion of the project is defined as the moment when manuscripts describing the project results are accepted for publication.

### Statistical strategy

5.3

Descriptive statistics will be used to summarize participant, classroom, and school characteristics; indoor air pollutant levels; microclimate parameters; biomarker concentrations; cognitive performance; and health outcomes.

To evaluate the impact of the intervention (vs. sham-intervention) and IAQ on longitudinal child outcomes, specifically cognitive performance and clinical/biological parameters (e.g., blood pressure), linear mixed-effects models will be applied. This model is specifically chosen to account for the longitudinal nature of the data, as multiple measurements will be collected from the same child. To handle the hierarchical clustering, random intercepts will be specified for school, class, and child. Background variables will be included as fixed-effect covariates in the models. Questionnaire data and clinical/pollution measurements will provide the necessary parameters to adjust for individual (e.g., socioeconomic factors and anthropometric measurements) and environmental (e.g., classroom pollution exposure, season) confounders, selected according to the requirements of each distinct analysis. Data collected from pre-sampling screening questionnaires will be used to adjust for building characteristics (e.g., building age, ventilation system) and external environmental factors (e.g., traffic exposure).

To analyze differences in environmental exposure levels (both external pollutants and internal exposure parameters) across different study phases (intervention vs. sham-intervention) and subgroups (e.g., schools), paired statistical tests (e.g., Student’s t-test, Mann–Whitney U test, or Wilcoxon signed-rank test) and ANOVA (or Kruskal-Wallis test, or Friedman test) will be used. The relationship between various parameters will be statistically analyzed using correlation and regression analysis.

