### Sample size calculation

2.2

A linear mixed-effects model will be applied to evaluate the association between the IAQ, the intervention, and the measured clinical parameters and biological biomarkers. Random intercepts will be specified for school, class, and child, and site-specific estimates will be combined through meta-analysis. As no pilot data were available across all sites, a simulation-based power analysis was conducted in R. The simulations assumed a within-person residual standard deviation (SD) of 1, and intra-class correlations (ICCs) of 0.05 for school, 0.10 for class, and 0.50 for child. For each scenario, 1,000 datasets were generated. In each dataset, the group × time contrast at the final time point was estimated using a linear mixed model, and site-specific results were combined via random-effects meta-analysis. The proportion of simulations yielding a two-sided *p* < 0.05 was recorded. Results indicated that recruiting approximately 150 children per country would provide 90% power to detect a medium-sized standardized intervention effect (Cohen’s d = 0.5 SD). This medium effect was selected as a pragmatic benchmark and should not be interpreted as the minimum clinically important difference for each outcome. We acknowledge that smaller effects than d = 0.5 SD may still be clinically or public-health relevant, but our study may have limited power to detect such smaller effects, and null findings should therefore be interpreted with caution.

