### Sampling timeline

2.3

The LEARN study consists of four phases and takes approximately 6 to 7 weeks to complete for each school (Figure 1).

Baseline Period (BaP): No intervention is implemented at baseline (1 week).The participating classes are randomly assigned to one of two sequences in the crossover design: either starting with the intervention phase (installation of air purification units with filters) followed by the control phase (sham-intervention with installation of air purification units without filters)(R1), or vice versa (R2). Randomization is performed at the class level using computer-generated random numbers. The study is single-blinded, hence participants and teachers are unaware of the assignment of the intervention phase.Intervention Period 1 (IP1): The assigned (sham-) intervention is implemented and administered over 2 weeks.Washout Period (WP): A washout period of 1 to 2 weeks follows IP1, ensuring that the acute environmental and physiological effects of the initial intervention are fully diminished to maintain a true crossover design (26–29). Furthermore, this timeframe accommodates the academic calendar and classroom scheduling constraints. Potential carry-over effects will be further evaluated and adjusted for in the statistical analysis.Intervention Period 2 (IP2): The intervention status switches between the two groups, and the second phase of the study is conducted.

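### The mixed model for this class-randomised crossover has no class-by-period component, so the standard error of the intervention effect is too small whenever classmates share class-specific variation within a period

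*Protocol article*

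**What the plan says.** All references are to the protocol article.

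- **Randomisation** (2.3 Sampling timeline): "Randomization is performed at the class level using computer-generated random numbers". A class receives the filter in one intervention period and the sham in the other.
- **Outcome timing** (4 Health outcomes): "The subsequent testing days occur on the final day of IP1 and the final day of IP2". Each intervention period therefore contributes one testing occasion.
- **Model, analysis section** (5.3 Statistical strategy): "To handle the hierarchical clustering, random intercepts will be specified for school, class, and child".
- **Model, sample size section** (2.2): "Random intercepts will be specified for school, class, and child, and site-specific estimates will be combined through meta-analysis".
- **Power simulation** (2.2): "The simulations assumed a within-person residual standard deviation (SD) of 1", with "intra-class correlations (ICCs) of 0.05 for school, 0.10 for class, and 0.50 for child". There is one class ICC and no component for class within period. The stated result is 90% power for 0.5 SD with about 150 children per country.
- **Period term** (4.3 Cognitive assessment): intervention period enters the mixed model as a covariate to deal with residual learning.

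The article names no class-by-period random effect, cluster-robust variance or class-level analysis. The random part is written out in the same form in two places, so this is a stated choice and not a detail left to an analysis plan.

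**The concern.** Treatment varies between periods within a class, so the unit that carries the treatment information is the class in a period. School, class and child intercepts are all constant across IP1 and IP2 and all drop out of the within-child difference. The stated model then treats the differences of classmates as independent.

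The period covariate removes only a shift common to all classes. It does not remove what one class experiences in one period, such as its room air, its activities or the conditions of its test session. The trial's own aim assumes that classroom air varies over time and affects the children who share it, so a class-by-period variance of exactly zero is hard to assume.

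The same model serves both primary outcomes, cognition and blood pressure. The error runs in one direction: intervals too narrow, and a chance difference between two class test days read as an effect of the purifier. The exposure-response models are affected in the same way, because classroom air is measured per class and period.

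**Working it through.** **Inputs from the article.** Residual SD 1; ICCs 0.05, 0.10 and 0.50; about 150 children in each of three countries; two-sided 5%; random-effects pooling of country estimates; at least two classes per school.

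**Assumptions, because the article gives no figure.** 8 classes of 19 per country (8 × 19 = 152), with 6 to 14 classes as the range. Class-by-period variance t is expressed as a fraction of the residual variance. DerSimonian-Laird is taken as the random-effects method.

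**Step 1: the plan's own figure.** For the group × time contrast (final against baseline, 75 against 75 children) with no class-by-period variance:

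SE = √[2 × 1 × (1/75 + 1/75)] = 0.231 per country.

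For an effect of 0.5 residual SD, DerSimonian-Laird pooling of three such estimates gives 90.9% power by simulation. This agrees with the stated 90%. In this contrast the intercepts cancel, so the number of classes plays no part.

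**Step 2: the SE error.** Take the IP2 − IP1 difference with residual variance 1 and class size m.

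- True variance of a class-mean difference: 2(t + 1/m).
- Variance under the stated model: 2(1 + t)/m.
- Ratio of SEs: √[(1 + mt)/(1 + t)].

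With m = 19:

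- t = 0.02: √(1.38/1.02) = 1.16
- t = 0.05: √(1.95/1.05) = 1.36
- t = 0.10: √(2.90/1.10) = 1.62

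**Step 3: type I error at nominal 5%.** The analytic value is 2[1 − Φ(1.96/ratio)].

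| t | SE ratio | Per country, analytic | Per country, simulated | After DerSimonian-Laird, simulated |
|---|---|---|---|---|
| 0 | 1.00 | 5.0% | 5.1% | 3.9% |
| 0.02 | 1.16 | 9.2% | 9.6% | 6.3–6.5% |
| 0.05 | 1.36 | 15.0% | 15.4% | 8.8–9.4% |
| 0.10 | 1.62 | 22.7% | 23.6% | 11.8–12.2% |

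At t = 0.01 the pooled rate is about 4.9%. Pooling dilutes the excess because part of it appears as heterogeneity between countries.

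**Step 4: is this range of t large?** Reading the ICCs as shares of total variance, the residual share is 1 − 0.65 = 0.35, and the class variance is 0.10/0.35 = 0.286 on the residual scale. Then t = 0.05 means that 0.05/0.286 = 17% of the class variance is specific to a period, a cluster autocorrelation of about 0.8.

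**Step 5: checks.** A fitted mixed model with the three stated intercepts and three time points rejected the null in 5 of 150 trials (3.3%) at autocorrelation 1, 89 of 600 (14.8%) at 0.8 and 159 of 600 (26.5%) at 0.5. Across 6 to 14 classes per country, autocorrelation 0.8 gives 11% to 20% per country and 7.5% to 11% pooled. A t-test on class-mean differences holds 4.8% to 5.2% per country.

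**Step 6: power of the stated contrast.** With 8 classes per country and autocorrelation 0.8, pooled power falls from about 91% to about 72% with the stated standard errors and about 67% with class-level ones.

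**The case against.** **The excess is conditional.** A reader might infer that false-positive rates exceed 5% as a matter of course. The article gives no class-by-period variance, and at 1% of residual variance the pooled test is still about nominal. This stands.

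**The per-country figures are not the final test.** Section 2.2 plans to combine country estimates by meta-analysis, so 6% to 12% is the relevant range for the overall result. Rates of 15% to 24% apply to a country's own estimate. This stands too.

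**School-wide influences may cancel.** Weather, outdoor pollution and school events look like obvious sources of trouble, but they act on all classes of a school at once. If classes in a school take opposite sequences, these effects drop out: error is 4.3% to 5.1% per country in simulation. Sections 2.3, 3.1.6 and 6.2 suggest such pairing, with two groups that switch, monitoring alternating between R1 and R2, and two classrooms compared. None states that sequences are balanced within school. Without balance, school-level variation inflates error, to about 6% to 10% after pooling.

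**Test conditions are controlled.** Testing takes place in a separate monitored room in a fixed morning window, and cognitive tests use recorded instructions, headphones and dividers. This argues against a large variance, not for a zero one. Section 5.3 also allows covariates such as season and classroom pollution. They may absorb some variation but are not a variance component, and classroom pollution lies on the causal path of the intervention.

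**The trial need not be underpowered.** That too might be inferred from Step 6, but it does not follow. The 90% refers to the group × time contrast. The within-child crossover contrast has SE √(2/150) = 0.115 per country. Inflated by 1.42 (the simulated ratio at autocorrelation 0.8) it is 0.164, and 0.164/√3 = 0.095 over three countries with no true heterogeneity. An effect of 0.5 is then still about 5 SEs.

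**Conclusion.** The point holds in conditional form. The stated random part does not match a design in which classes are randomised and switch treatment between periods, and any class-specific variation within a period makes the standard error too small. Under the assumptions in the working, type I error is about 10%, 15% and 24% per country and about 6%, 9% and 12% after pooling. At zero variance it is nominal per country and slightly conservative after pooling (3.9%).

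The algebra is certain. The size is not, because it rests on an assumed number of classes, class size and variance. Whether school-wide variation adds to the problem depends on balance within schools, which the article leaves open. The 90% power is reproducible, but in a calculation that sets this variance to zero. The absence of a named degrees-of-freedom method is not an error in an article of this kind.

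**What to change.** 1. Add a class-by-period random effect to the intervention and exposure-response models. State whether sequences are balanced within school. If they are not, add a school-by-period effect as well.
2. Use small-sample degrees of freedom, or analyse class-level period differences.
3. Carry the small-sample correction through the pooling. With 8 classes per country, class-level standard errors combined by DerSimonian-Laird with a normal test still gave about 8% error. Hartung-Knapp pooling held about 5%, but with power of only 52% for the stated contrast even at zero class-by-period variance. A single class-level t-test over all 24 classes held 4.7% to 5.3%.
4. Rerun the power simulation with a stated number of classes and a non-zero class-by-period component, for the contrast that the analysis will use, and restate the 90%.

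No new data are needed. The costs are wider intervals and lower stated power for the group × time contrast. With few classes per country the new variance may be estimated at its zero boundary. The class-level analysis is the fallback in that case and should be named in advance.
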